
#### Participant retention

Participants will receive SGD30 at each assessment for successfully completing assessments within their respective window periods. Participants in the usual care arm and the DMP incentive arm will receive SGD150 and SGD70, respectively, as forms of “fairness” payouts for not receiving the DMP and/or incentives entitled to other arms. Table 3 lists the participant payouts by arm.

**Table 3 Tab3:** Participant payouts

Type of payout	Condition	Payouts		
		Arm 1 (Usual care)	Arm 2 (DMP)	Arm 3 (DMP plus M-POWER)
Attending training session	Attend the training session	SGD10	SGD10	SGD10
Completing assessments	Complete assessments at Months 6, 12, 18, and 24 within their respective window periods	SGD30 per assessment	SGD30 per assessment	SGD30 per assessment
Study device data upload	Each device (pedometer, glucometer, and pill tracker) needs to contain at least one entry within the first 7 calendar days from the first Monday (inclusive) of the month to receive payouts for that device for that month The data must be uploaded successfully	NA	SGD2 per device per month^a^	SGD2 per device per month^a^
M-POWER Rewards	As per M-POWER Rewards scheme (Tables 1 and 2)	NA	NA	Max 1000 M-Points (SGD1000) over 104 weeks
Fairness payout	Complete both Month 12 and Month 24 assessments within their respective window periods Awarded upon completion of the Month 24 assessment	SGD150 for entire study^b^	SGD70 for entire study^c^	NA

^a^SGD6 per month for three devices (pedometer, glucometer, and pill tracker) in total

^b^For not receiving DMP, incentives for study device data upload, and M-POWER Rewards

^c^For not receiving M-POWER Rewards

Participant burden will be minimized by limiting participant in-person visits to five sessions (one baseline and four follow-up assessments), although additional visits may be necessary to disburse cash payouts or provide replacement devices. Malfunctioned or misplaced devices will be replaced at a subsidized rate (depending on budget) to enable continued participation of participants in the intervention arms.

#### Participant withdrawal and discontinuation

Participants are free to withdraw from the study at any time by informing the study team or the investigators of their decision to withdraw. Data that has been collected until the time of their withdrawal will be stored and analyzed. Participants may be discontinued from the study due to one or more of the following reasons:
They become pregnant.Upon voluntarily informing their doctor that they are participating in this study, their doctor decides that continuing participation could be harmful and informs us in the process.They fail to follow the instructions of the study team or investigators.

Participants who develop any of the exclusion criteria 2–13 during the course of the study will not be withdrawn from the study unless they choose to withdraw voluntarily. There are no concomitant care or other interventions that will be prohibited during the study.

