#### Data for sensitivity analysis and cost-effectiveness analysis

Medical data such as HbA_1c_ test results taken during usual care at the clinics and diabetes medications prescribed and purchased, including insulin initiation dates, will be obtained from the medical records and pharmacy bills of all participants. HbA_1c_ test results from these medical records will be used in sensitivity analyses. Billing data from inpatient, outpatient, pharmacy, and emergency departments will be collected to estimate net costs and cost offsets for the cost-effectiveness analysis. The costs of program delivery will be determined by capturing data on all relevant (non-sunk) labor costs, materials and supplies, contracted services (including costs for GlycoLeap), and M-POWER Rewards payouts.

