#### Study devices and apps

To encourage participants in the incentive arms to engage with the study components, weekly inactivity notifications that list the components that they have not been engaging with will be emailed to participants. Participants who are not engaging with the study components will be contacted by the study team, who will offer their assistance and ensure that participants are not experiencing problems with the devices or apps. Study team members will also note those who indicate that they do not wish to perform any activity(s) and will not contact these participants for the purpose of troubleshooting. At each follow-up assessment, study team members will also verify that participants are using the devices as instructed and respond to any queries that participants might have on usage of the devices or apps. Besides the aforementioned measures to reduce data loss, participants in both intervention arms will be incentivized to upload their data: participants will be given SGD2 per device per month for syncing their pedometers, glucometers, and pill trackers with their anonymous study accounts see (Table 3).

As participants in the DMP plus M-POWER arm may be tempted to cheat in order to earn more M-Points, they will sign a participant oath at the end of the training session and each time they collect their M-Points redemption payouts. This might help to improve data validity, as such oaths could reduce the likelihood of cheating [24]. The study team will also manage and back up data from the devices and apps and regularly check the data for inconsistencies that may suggest cheating.

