#### Primary analysis

Mean change in HbA_1c_ level at Month 12 is the primary outcome. The primary analysis will be performed on a modified intention-to-treat population, including participants who have both baseline and Month 12 HbA_1c_ level data. A linear regression model with HbA_1c_ level at Month 12 as the dependent variable and an intercept, HbA_1c_ level at baseline (continuous variable), indicator variables for participants who received DMP alone and participants who received DMP plus M-POWER, and indicator variables for stratification factors (gender and diabetes center) as independent variables will be performed. Using this model, a test for the global null hypothesis of all three arms having equal mean HbA_1c_ level at Month 12 will be performed (Null Hypothesis 1: Coefficient of DMP plus M-POWER = Coefficient of DMP = 0), followed by tests for three pairwise hypotheses, comparing mean HbA1c level at Month 12 in DMP alone vs. usual care (Null Hypothesis 2: Coefficient of DMP = 0), DMP plus M-POWER vs. usual care (Null Hypothesis 3: Coefficient of DMP plus M-POWER = 0), and DMP plus M-POWER vs. DMP alone (Null Hypothesis 4: Coefficient of DMP plus M-POWER = Coefficient of DMP). We will also conduct a sensitivity analysis with further adjustment for dichotomized HbA1c levels at baseline (7.5–9.2% vs. 9.3–11.0%). The differences in the primary outcome between study arms will be presented along with corresponding 95% confidence intervals. Following the closed testing procedure [32] for controlling for multiple comparisons involving three groups, only if tests of both the global null hypothesis and a pairwise null hypothesis reach statistical significance at the 0.05 level will the pairwise null hypothesis be rejected.

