If there are substantially different drop-out rates or different drop-out patterns among the three arms, a general linear model for repeated measures will be performed for the primary analysis. This model simultaneously models HbA_1c_ level at baseline, Month 6, and Month 12 as the dependent variables and includes interactions between indicator variables for DMP alone and Month 6 visit, DMP plus M-POWER and Month 6 visit, DMP alone and Month 12 visit, and DMP plus M-POWER and Month 12 visit as independent variables. The model will also adjust for visit (indicator variable for the Month 6 visit and indicator variable for the Month 12 visit) and randomization stratification variables (gender and diabetes center). An unstructured matrix will be used to model the residual variance-covariance structure within participant. The model does not include main effect terms for the intervention variables, and thus it constrains the estimated group means of baseline HbA_1c_ levels to be identical across the three randomized groups. This model specification helps control for the variation in baseline HbA_1c_ level arising by chance among the randomized groups. Using this model, a test for the global null hypothesis of all three arms having equal mean HbA_1c_ level at Month 12 will be performed (Null Hypothesis 1: Coefficient of interaction between indicator of DMP alone and indicator of Month 12 visit = Coefficient of interaction between indicator of DMP plus M-POWER and indicator of Month 12 visit = 0), followed by tests for three pairwise hypotheses, comparing mean HbA_1c_ level at Month 12 in DMP alone vs. usual care (Null Hypothesis 2: Coefficient of interaction between indicator of DMP alone and indicator of Month 12 visit = 0), DMP plus M-POWER vs. usual care (Null Hypothesis 3: Coefficient of interaction between indicator of DMP plus M-POWER and indicator of Month 12 visit = 0), and DMP plus M-POWER vs. DMP alone (Null Hypothesis 4: Coefficient of interaction between indicator of DMP alone and indicator of Month 12 visit = Coefficient of interaction between indicator of DMP plus M-POWER and indicator of Month 12 visit). If the missing data patterns do not necessitate using a general linear model for repeated measures as a primary analysis, this analysis will be conducted as a sensitivity analysis.

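### Discontinuing participants from the study for not following instructions, with a primary analysis limited to those with a Month 12 HbA1c, can select on adherence after randomization

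*Protocol article*

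**What the plan says.** The section Participant withdrawal and discontinuation introduces its list with "Participants may be discontinued from the study due to one or more of the following reasons". The third reason is "They fail to follow the instructions of the study team or investigators". What ends is participation in the study, not only the intervention. No threshold, warning step or adjudication is given. On data, the section says of those who withdraw: "Data that has been collected until the time of their withdrawal will be stored and analyzed". It does not say whether a discontinued participant is still invited to the Month 6 to 24 assessments. It does keep participants who later develop most of the exclusion criteria, but gives no such protection to those who do not follow instructions.

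Primary analysis defines the analysis set as a "modified intention-to-treat population, including participants who have both baseline and Month 12 HbA_1c_ level data". It then adds a fallback: "If there are substantially different drop-out rates or different drop-out patterns among the three arms, a general linear model for repeated measures will be performed". If that condition is not met, the repeated-measures model is a sensitivity analysis.

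Under Data management and monitoring, Study devices and apps, "Participants who are not engaging with the study components will be contacted by the study team". Staff also check device use at each follow-up assessment. Those who decline an activity are recorded and receive no further troubleshooting calls; the section does not call for their discontinuation.

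Clinic HbA1c values are collected for all participants, and "HbA_1c_ test results from these medical records will be used in sensitivity analyses".

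**The concern.** The trial asks what adding the package, with or without rewards, to usual care does to HbA1c. Adherence is the route by which the package works, and the rewards were added because self-care declined over 24 weeks in the feasibility study. Low engagement is therefore foreseeable, and a rule that can end participation for it acts on a variable that the intervention itself affects.

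The trial is open-label. Usual-care participants receive recommendations only. Arms 2 and 3 also receive a pedometer, glucometer, pill tracker and apps, with syncing requests and staff checks, so a failure to follow instructions is much easier to see there. If the rule is used before Month 12 and no study sample is taken afterwards, the participant leaves the primary analysis. The comparison would then no longer be of the groups as randomized. The cost-effectiveness ratios, which use the Month 12 HbA1c difference, would inherit the same selection.

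**Working it through.** **Design figures.** Sample size gives SD 1.2, baseline to Month 12 correlation 0.2, difference 0.5, 90 per group, 20% attrition, 113 per arm and 339 in total.

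- Residual SD after baseline adjustment: 1.2 × √(1 − 0.2²) = 1.176.
- Required n per group: 87 by the normal approximation, 88 by the noncentral t. At 90, simulated power of the closed test is 81.1% for each adjacent contrast, so the stated figure is reproduced.
- 90 / 0.8 = 112.5, rounded up to 113; 3 × 113 = 339. The allowance covers 113 − 90 = 23 losses per arm from any cause.
- Standard error of a pairwise contrast at 90 per group: 1.176 × √(2/90) = 0.175.

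The sample size is sound and is not at issue.

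**Illustration 1: least adherent fraction p removed from one arm only.** The documents give no discontinuation rate and no correlation r between adherence and the Month 12 residual. Both are assumed. With z the normal quantile cutting off p and φ the normal density, the arm mean shifts by r × 1.176 × φ(z)/(1 − p).

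| p removed | φ(z)/(1 − p) | r = 0.2 | r = 0.4 |
|---|---|---|---|
| 5% | 0.109 | 0.026 | 0.051 |
| 10% | 0.195 | 0.046 | 0.092 |
| 15% | 0.274 | 0.065 | 0.129 |

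The shift is toward lower HbA1c in the arm that loses participants. At 5% it is at most 0.051/0.175 = 0.3 standard errors; at 15% and r = 0.4 it is 0.129/0.175 = 0.7. In heads, 15% of 113 is about 17 people discontinued on this one ground.

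**Illustration 2: two classes, benefit only in adherers.** Assume a true difference from usual care of −0.5 and no benefit in non-adherers, who make up all of those removed. The estimate becomes −0.5/(1 − p): −0.53, −0.56 and −0.63 for p = 5%, 10% and 20%, a bias of 0.03, 0.06 and 0.13.

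**Illustration 3: no true effect.** Let adherers have HbA1c lower by g = 0.3 to 0.5 whatever their arm, and let 20% of each arm be non-adherent. Removing p from an intervention arm only gives a bias of 0.8 × g × [1/(1 − p) − 1]. That is 0.01 to 0.02 at p = 5% and 0.06 to 0.10 at p = 20%. With equal removal in all arms it is 0.

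**Illustration 4: DMP plus Rewards against DMP.** Assume 20% and 40% non-adherent and an effect of 0.8 in adherers.

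- As randomized: −0.8 × 0.8 + 0.8 × 0.6 = −0.64 + 0.48 = −0.16.
- Half the non-adherers removed: −0.64/0.9 + 0.48/0.8 = −0.71 + 0.60 = −0.11.
- All removed: −0.8 + 0.8 = 0.

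If rewards raise adherence, the rule removes more from the DMP arm and the bias runs against Rewards.

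**The case against.** A reader might infer that the rule will remove non-adherers and that the result will always be tilted toward the interventions. The documents support neither.

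The rule is permissive. The article's specific account of non-engagement points toward keeping people: staff offer help, record refusals and stop calling. Participants are to remain in their arms for 24 months, and lost or broken devices are replaced so that they can continue. Most activities are recommended or encouraged, so low adherence is not clearly a failure to follow instructions, although device use is checked against instructions. The direction is not fixed either: Illustration 4 reverses it for one of the three pairwise hypotheses, and Illustration 3 gives zero when removal is equal and there is no effect. The upper figure of 0.13 rests on two unsourced assumptions at their extremes. The article condenses a longer protocol, so the absence of a Month 12 value after discontinuation is an inference from its silence on later visits. All of this stands, and it limits the claim to what the rule can do.

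The plan also has two safeguards. The repeated-measures model keeps baseline and Month 6 values and becomes primary if drop-out differs substantially between arms. Clinic HbA1c is available for a sensitivity analysis. They help but do not close the gap. The trigger for the model is not defined. The model conditions on HbA1c, visit, arm by visit, gender and center, but not on engagement, which would drive the removal. A participant discontinued before Month 6 contributes only a baseline value. The clinic values do not enter the primary analysis. Nor does the practice of leaving non-engagers alone override the discontinuation rule; if they are meant to stay, the rule as worded is not needed.

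**Conclusion.** The point holds in a limited form. A discretionary rule without criteria, which ends study participation for failing to follow instructions, combined with a complete-case primary analysis, can select on adherence after randomization. It can act unequally because device and app use is checked only in Arms 2 and 3. For each DMP arm against usual care the likely bias favours the intervention; for DMP plus Rewards against DMP it may run the other way.

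The size cannot be known from the documents. Under the assumed correlation of 0.2 to 0.4 and 5% to 15% removed from one arm, it is about 0.03 to 0.13 points against the 0.5 design difference. It is near zero if the rule is hardly used. The reason to act is that a Month 12 study sample not taken cannot be recovered later, while the change in wording is small.

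**What to change.** Delete failure to follow instructions as a ground for ending study participation, or limit it to ending contact about the intervention. State that such participants stay in HbA1c follow-up at Months 6, 12, 18 and 24 unless they withdraw consent, and that they are analysed in their randomized arm. This point does not bear on the pregnancy and physician-decision grounds, and no change to them is asked for.

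The cost is a short amendment and a few more assessment visits, with the SGD30 payment per completed assessment that Table 3 already provides for participants in every arm. The sample size stays at 113 per arm. The amendment should be in place before the rule is first applied.

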#### Adverse event reporting

Before commencing the study, participants will be informed that they should report the occurrence of any potential adverse events during the course of the study to the study team. The study team will ask participants about potential adverse events during the follow-up assessments. In the event that the study team is informed of any serious adverse event (SAE), the principal investigator will notify the SingHealth Centralized Institutional Review Board (CIRB) by submitting the SAE Reporting Form within the stipulated time frame. The notifying and reporting requirements depend on the severity, nature and causality of the event, and specific procedures as delineated by SingHealth will be followed [33]. SAEs will also be reported to the National University of Singapore Institutional Review Board (NUS-IRB).

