### Participant timeline and study arms

Interested patients will be directed to take an online screener questionnaire to assess their eligibility to join the study. All eligible patients will be invited to complete an online baseline questionnaire and attend a training session conducted by the study team where they will be briefed on the study and will sign an informed consent form (i.e., enrollment). During the training session, participants will have their baseline anthropometric measurements taken by the study team, their blood drawn by trained phlebotomists for HbA_1c_ tests, and their arm allocation revealed to them (i.e., recruitment). All patients will receive arm-specific participant booklets containing information about the study design, timeline, visits, recommended activities, interventions, and payouts. Participants in both intervention arms will receive the DMP along with training on how to use the study devices and apps. In addition, participants in the DMP plus M-POWER Rewards arm will be given details about the M-POWER Rewards program and will sign a participant oath declaring that all activity data that they will provide solely represents their own efforts without attempts to cheat. Research has revealed that such oaths might reduce the probability that individuals will engage in dishonest behavior [24].

Participants will remain in their respective study arms throughout the 24-month (104-week) study. Follow-up questionnaires and assessments will be administered within 8-week window periods at Month 6 (Weeks 22–29), Month 12 (Weeks 48–55), Month 18 (Weeks 74–81), and Month 24 (Weeks 100–107). All follow-up assessments will be conducted at Duke-NUS Medical School (or other study venues, if available) where anthropometric measurements will be taken and blood samples collected for HbA_1c_ tests.

Figure 2 illustrates the flow diagram for study participants.

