### Sample size

Data from Bilger et al. [31] showed a standard deviation (SD) of HbA_1c_ levels averaged across usual care and intervention groups being 1.2% at both baseline and after a 6-month intervention and a correlation of 0.4 between the two time points. We assume an SD of 1.2% in HbA_1c_ at Month 12 (primary endpoint) and a correlation of 0.2 between baseline and Month 12 measurements. In order to detect a mean difference of 0.5% between the usual care and DMP arms and 0.5% between the DMP and DMP plus financial incentive arms, with analysis of covariance (ANCOVA) adjustment for baseline HbA_1c_ and multiplicity adjustment by the closed testing procedure [32], a sample size of 90 per group is needed to have 80% power at a two-sided 5% familywise type 1 error rate. To allow for 20% attrition at Month 12, we will recruit 113 patients per arm, or 339 in total.

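### Adverse events are learned of mainly by participant report under unequal between-visit contact, while hospital data collected for every arm have no stated safety use

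*Protocol article*

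**What the plan says.** The section Adverse event reporting gives two routes. Before the study starts, "participants will be informed that they should report the occurrence of any potential adverse events during the course of the study to the study team". Later, "The study team will ask participants about potential adverse events during the follow-up assessments". Reporting of a serious event to the ethics boards begins once the study team has been told of it; no search of records for events is described. The section Participant withdrawal and discontinuation implies a third, occasional route: a participant may be discontinued if, having been told about the study, "their doctor decides that continuing participation could be harmful and informs us in the process".

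Study design describes the trial as open-label. Contact between visits differs by arm. Arms 2 and 3 have 24 weeks of coaching through the app (section on Arm 2). Under Data management and monitoring, Study devices and apps, there are weekly inactivity emails, and "Participants who are not engaging with the study components will be contacted by the study team". No comparable contact is described for Arm 1.

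On hospital data, the section Data for sensitivity analysis and cost-effectiveness analysis says: "Billing data from inpatient, outpatient, pharmacy, and emergency departments will be collected to estimate net costs and cost offsets for the cost-effectiveness analysis". Secondary cost-effectiveness analyses computes net costs for each arm, so the data must cover all three. Data management and monitoring gives the DSMB oversight of participant safety.

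**The concern.** Spontaneous reporting depends on having an occasion to report. Someone who exchanges messages with a coach or is telephoned about an idle device has more occasions than someone whose only described contact is an assessment every six months. The team that receives the reports also knows the arm. If reporting differs, the safety counts by arm mix true risk with opportunity to report.

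Missed assessments are the second gap. A person who misses a visit is not asked at that visit, and an event may go unrecorded if it is not volunteered or recalled later.

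What is at stake is the DSMB's ability to read a difference in serious events. More reporting in Arms 2 and 3 could look like harm, and poorer capture there could hide it. The article itself treats increased physical activity as a possible risk, since it screens for it with the PAR-Q. It also keeps in the study participants who develop conditions such as stroke or cardiovascular disease.

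**Working it through.** The article states no adverse event rate, count or safety power, so there is no safety figure to reproduce. The check sets the sources side by side and then shows what unequal capture would do.

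**Sources by arm**

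| Source | Arm 1 | Arms 2 and 3 |
|---|---|---|
| Question at follow-up assessments | 4 | 4 |
| Spontaneous report to the team | any time | any time |
| Coaching contact | none described | 24 of 104 weeks |
| Outreach about device use | none described | non-engagers only |
| Inactivity emails | none described | weekly, listing unused components (the article says incentive arms) |
| Device-use check at assessments | none described | yes |
| Inpatient and emergency billing | collected | collected |

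The solicited route is scheduled identically. The difference lies in the spontaneous route between visits. The billing data are the one source in the table that depends neither on contact with the study team nor on attendance.

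**Missed assessments.** The Sample size section recruits 113 per arm "To allow for 20% attrition at Month 12". This reproduces: 90 / (1 − 0.20) = 112.5, rounded up to 113, and 3 × 113 = 339. The plan therefore allows for about 0.20 × 113 = 22.6, or 23, participants per arm with no Month 12 assessment. The Primary analysis section provides for dropout that differs by arm. Inducements to attend differ too. Table 3 offers SGD150 in Arm 1 and SGD70 in Arm 2 for completing both the Month 12 and Month 24 assessments. Table 2 offers Arm 3 up to 60 M-Points at each assessment. Unequal reach of the solicited question is therefore possible in either direction.

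**Illustration, with assumed inputs.** Let the true risk p of an event be equal in all arms, with capture probability d1 in Arm 1 and d2 in Arm 2 or 3, and n = 113 per arm.

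- Expected recorded participants with an event: n·p·d1 and n·p·d2.
- Apparent risk ratio: d2/d1, whatever the value of p.
- Chance of a spurious two-sided 5% result in the direction of d2 > d1: Φ((p2 − p1 − 1.96·√(2p̄(1 − p̄)/n)) / √((p1(1 − p1) + p2(1 − p2))/n)), with p1 = p·d1, p2 = p·d2 and p̄ their mean.

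Worked line for p = 20%, d1 = 0.6, d2 = 0.8: p1 = 0.12, p2 = 0.16, p̄ = 0.14. The pooled standard error is √(0.2408/113) = 0.0462, and 1.96 × 0.0462 = 0.0905. The unpooled standard error is √(0.2400/113) = 0.0461. Φ((0.04 − 0.0905)/0.0461) = Φ(−1.095) = 0.137.

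| d1 | d2 | Risk ratio | Expected, p = 10% | Chance | Expected, p = 20% | Chance |
|---|---|---|---|---|---|---|
| 0.7 | 0.7 | 1.00 | 7.9 vs 7.9 | 2.5% | 15.8 vs 15.8 | 2.5% |
| 0.7 | 0.8 | 1.14 | 7.9 vs 9.0 | 4.7% | 15.8 vs 18.1 | 6.2% |
| 0.6 | 0.8 | 1.33 | 6.8 vs 9.0 | 8.5% | 13.6 vs 18.1 | 13.7% |
| 0.5 | 0.9 | 1.80 | 5.7 vs 10.2 | 21.7% | 11.3 vs 20.3 | 41.0% |

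If Arm 1 were the better captured arm, the ratios would invert (0.7/0.8 = 0.88, for example). None of p, d1 or d2 comes from the article. The table shows sensitivity and estimates nothing.

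**The case against.** The strongest reply is that the only stated enquiry takes place at four assessments common to all arms, and that adverse events are not a listed outcome and no between-arm comparison of them is planned. Unequal contact then matters only for events volunteered between visits that would not have surfaced at the next one. This stands, and it is why the point is put as a risk. The article is also condensed: it refers to an ethics-approved protocol, hospital-group reporting procedures and a DSMB charter that are not shown and may say more.

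Several stronger readings are tempting and are not supported:

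- A reader might infer that the counts are biased. That needs capture probabilities the article does not give.
- A reader might count up to 104 weekly contacts as occasions for detection. The emails list unused components, outreach goes only to non-engagers and stops for activities they decline, and coaches have no stated adverse event role.
- A reader might take the 20% attrition as people who are never asked. It is a sample-size allowance at Month 12, and someone who misses that visit may be asked at another.
- A reader might say events come only from participants, or that billing is reserved for costing. The article does not restrict who may inform the team of a serious event, a doctor may do so, and no other use of the billing is excluded.
- A reader might want events learned through coaching or calls left out of the comparison. That would remove events from Arms 2 and 3 that might also have been reported at the next assessment, while Arm 1 would lose none, so harm in the intervention arms would be undercounted.

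Billing is not perfectly neutral either. Arm 3 rebates cover approved non-inpatient expenses and are meant to encourage use of care, so emergency visits might respond to the arm. Admissions are less exposed to this, though elective ones are not adverse events.

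**Conclusion.** The point holds as a risk. Capture rests mainly on participant report in an open-label trial with unequal between-visit contact, so serious event counts by arm are open to ascertainment bias of unknown size and direction. Events in people who miss assessments may also be missed. Over the assumed range above, the apparent risk ratio under equal true risk runs from 1.00 to 1.80, and it would fall below 1 if Arm 1 were better captured. It is 1.00 if capture is equal. A more arm-neutral source is already collected for every arm, with costing as its only stated use. Adding a safety use is worthwhile because it costs little and reaches participants who miss visits without withdrawing. The primary HbA1c analysis is not affected.

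**What to change.** In Adverse event reporting and in Data for sensitivity analysis and cost-effectiveness analysis:

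1. Add safety as a stated use of the inpatient and emergency data. For all participants who have not withdrawn, search these records over the same window in every arm (for example, randomization to Week 107, the end of the Month 24 window) for serious events not already reported.
2. Give the DSMB the result by randomized arm. Show hospital admissions separately from emergency visits, and elective admissions separately where the records allow.
3. Ask the adverse event question in the same way at the four assessments in all arms.
4. Record how each event was first learned of, and keep every event in the counts. Any between-arm comparison can be shown twice: for all events, and for events found at an assessment or in the records. An event first learned of through other contact counts in the second set if it was also found at an assessment or in the records.

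The cost is some protocol wording, the record search and one tabulation from data already being collected. The downside is small: billing data arrive late and may miss care outside the covered institutions, so expedited reporting to the ethics boards still relies on the team being informed.
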